## Abstract

**Background:**

Opioid use disorder (OUD) is a major public health issue and recovery is a long-term and complex process. Opioid Agonist Treatment (OAT) including medications such as methadone and buprenorphine, is the first-line medical intervention for OUD, however clinical responses among sub-populations differ and concurrent heroin use among individuals in OAT is reported. Contingency management (CM) is a behavioural intervention involving the application of positive reinforcement (e.g., monetary incentives) contingent upon evidence of positive behaviour change. CM is based on the theoretical principles of operant conditioning and is among the most efficacious psychosocial intervention in promoting substance use-related behaviours, including abstinence from smoking, alcohol and illicit drugs, medication adherence, vaccination uptake and attendance. Technology can be leveraged to expand the reach and accessibility of these interventions, automating key components of intervention delivery, including objective behaviour monitoring and immediate reward delivery. Currently, there are no fully remote CM interventions specifically targeting heroin use among individuals undergoing treatment for OUD, highlighting a critical need for innovation in addressing this complex aspect of substance use. Developing and delivering a fully digitalised app-based CM intervention for reducing heroin use among individuals in treatment for OUD holds considerable potential. This paper provides a protocol for a feasibility study that aims to determine the acceptability and feasibility of conducting a future randomised controlled trial of the clinical effectiveness of app-based CM to encourage heroin abstinence among clients receiving OAT in UK drug treatment services.

**Methods:**

Forty OAT service users in UK drug treatment services who continue to use heroin will be randomly assigned to either (1) OAT plus a smartphone app providing abstinence incentives or (2) standard OAT alone. Participants in the intervention arm will receive financial incentives contingent on heroin-negative toxicology results. Over a 12-week period, participants will receive thrice-weekly push notifications via the smartphone app when an oral saliva test is due. Participants will receive feedback upon submission and verified heroin-negative tests will result in notification of earnings. The primary outcome of this feasibility trial is the number of eligible service users recruited over the 6-month recruitment period. Other feasibility outcomes include intervention adherence, drug screening completion and follow-up rates. Acceptability will be explored among both clinicians and service users. Progression to a larger confirmatory trial will be evaluated based on the pre-specified progression criteria.

**Discussion:**

Research on CM has grown exponentially over the last decade, with remote technologies being leveraged more than ever to expand the reach and scope of these interventions. This study will evaluate the feasibility of a mCM app to support heroin abstinence among OAT recipients. By integrating CM with mobile technology, this approach could enhance treatment accessibility and effectiveness, potentially improving outcomes for a high-risk population.

## Introduction

Opioid use disorder (OUD) is a major public health issue and recovery is a long-term and complex process, with the average time in treatment for opiate problems around two years longer than for other substances [1]. Deaths globally from opioid overdose continue to rise, exceeding 125,000 and accounting for approximately 25% of all drug-related deaths [2]. Half of adults receiving treatment in the UK for substance use are there for problems with opiates. Opioid Agonist Treatment (OAT) including medications such as methadone and buprenorphine, is the first-line medical intervention for OUD. These treatments are strongly supported by evidence showing their effectiveness in lowering mortality and substance use, enhancing physical and mental health, reducing criminal activity, and mitigating HIV risks and associated behaviours [3].

Despite the well evidenced effectiveness of OAT, clinical responses among sub-populations differ and concurrent heroin use among individuals in OAT is reported. In England, the rate of illicit opiate abstinence after three and six months of OAT was estimated as 46% and 48%, respectively [4]. Several risk factors are associated with continued heroin use during OAT, including suboptimal doses [3], little to no psychological therapies [5] and personal situations and environments including continued connections with drug using peer groups [6,7]. Continued heroin use is associated with high treatment drop-out rates, underscoring the need for comprehensive and innovative interventions to address this complex issue [8].

Contingency management (CM) is a behavioural intervention involving the application of positive reinforcement (e.g., monetary incentives) contingent upon evidence of positive behaviour change. CM is based on the theoretical principles of operant conditioning and is among the most efficacious psychosocial intervention in promoting substance use-related behaviours, including abstinence from smoking, alcohol and illicit drugs [9–15], medication adherence [16,17], vaccination uptake [18] and attendance [19]. CM targeting opioid abstinence in service users undergoing treatment for OUD was associated with a medium-large effect size on abstinence versus a control intervention [17].

Despite CM’s well-established research evidence base and the UK’s National Institute for Health and Care Excellence (NICE) recommendation to evaluate and integrate it into addiction services, the UK has a limited track record of applying these interventions. One potential solution to significantly expand access to CM while minimising the strain on resources and staff is the remote delivery of CM. The challenges of implementing CM in real-world settings, particularly in regions with budget constraints and logistical barriers such as UK drug and alcohol treatment services, have been well-documented [20–23]. Technology offers a way to overcome these challenges by automating key components of the process, such as objective behaviour monitoring and immediate reward delivery, thereby ensuring treatment fidelity while alleviating pressure on overburdened healthcare systems [24].

Previous work undertaken by the research team and others, suggests that digital CM is feasible, acceptable and effective in promoting positive behaviour change, including adherence to prescribed medications [25,26], clinical appointment attendance [25] and abstinence from alcohol [27–33], smoking [33–40] and other substances [25,41]. High levels of acceptability towards remote monitoring of behaviour and delivery of reinforcement among service user recipients [42,43] and non-recipients [44] were also found, with 81% reporting to be in favour of incentive programmes. Importantly, 96% of service users owned a mobile telephone (85% of which were smartphones), suggesting it is a potentially viable approach. Consultations with policy and clinical stakeholders have provided further support for the development and implementation of these interventions within UK drug and alcohol treatment services [45].

However, a significant gap exists in the space of opioid use. Currently, there are no fully remote CM interventions specifically targeting heroin use among individuals undergoing treatment for OUD, highlighting a critical need for innovation in addressing this complex aspect of substance use. Developing and delivering a fully digitalised app-based CM intervention for reducing heroin use among individuals in treatment for OUD holds considerable potential. This novel approach has the capacity to significantly broaden the scope and reach of CM treatment, supporting clients undergoing OAT to reduce and abstain from continued heroin use. This paper provides a protocol for a feasibility study that aims to determine the acceptability and feasibility of conducting a future randomised controlled trial of the clinical effectiveness of app-based CM to encourage heroin abstinence among clients receiving OAT in UK drug treatment services.

## Methods

This study was prospectively registered (ISRCTN60538178) and has been reviewed and given favourable opinion by West Midlands – South Birmingham Research Ethics Committee (24/WM/0216). We report this protocol (V1.2, 8.1.25) using the SPIRIT guidelines for reporting of intervention trials (see Supporting Information). Protocol amendments will be agreed and approved by the sponsor and REC. The project is currently in development phase and due to commence recruitment on 1^st^ July 2025. Last participant will be recruited on 31^st^ December 2025 and data collection completed by 25^th^ March 2026. Results are expected to be available by 1^st^ December 2026.

### Aims and objectives

This study aims to determine the acceptability and feasibility of conducting a future randomised controlled trial of the clinical effectiveness of app-based Contingency Management (mCM) to encourage heroin abstinence among clients receiving OAT in UK drug treatment services.

Feasibility study objectives are as follows:

Primary objective:

Determine the number of eligible service users and recruitment rates.

Other objectives are to:

Determine adherence to the intervention (e.g., user engagement, responses to prompts, uploads);Determine follow-up rates at 12 weeks;Explore intervention acceptability among participants (including those not receiving the mCM intervention);Explore intervention acceptability among treatment providers;Determine app usability using the System Usability Survey [46];Explore the suitability and participant acceptability of objective measures for the primary clinical outcomes (i.e., heroin abstinence);Characterise aspects of the primary outcome needed for a sample size calculation for a larger trial (including an estimate of the intraclass correlation).

### Design and setting

The feasibility study will use an individually randomised controlled design, where service users will be recruited and randomly assigned (1:1) to one of the conditions below over a 12-week period:

AmCM (app-based CM + OAT): Smartphone App plus incentives for objective verification of heroin abstinenceBTAU: Treatment as Usual (OAT only)

The trial design has been created to reflect the future confirmatory trial in which the novel intervention “Mobile Contingency Management” (mCM) will be compared to a control condition (TAU) in which no CM will be received.

Two sites will be recruited: one from South London and the Maudsley NHS Foundation Trust (SLaM NHS) and one from a non-NHS service. Drug services will be eligible if they provide treatment to individuals with OUD.

To advise on all aspects of study design and implementation, a PPIE group was convened. During both study conception and app design, we consulted with the PPIE group, who highlighted positive feedback on CM for drug abstinence and remote testing benefits like independence. Participants liked the app’s simple design and potential to aid behaviour change. Discussions about intervention specifics, including incentive magnitude, testing window and clinician involvement will be continued. The PPIE group will be given the opportunity to engage with the app and provide feedback once developed. The group will be consulted with at key points during the trial.

### Eligibility

The eligibility criteria for enrolling service user participants will include:

Receiving OAT (methadone or buprenorphine, including pro-longed release);Self-reported heroin use at least 1 day/week;Aged ≥ 18 years;Able to operate an Android or iOS smartphone with acceptable capability;Willing to receive 12-week CM intervention;Able to provide informed consent.

Service users will be excluded if currently participating in any other research studies.

### Recruitment

Service users (n = 40) receiving OAT who continue to use heroin will be recruited over 6 months (July to December 2025). Individuals will be identified by their keyworker at participating clinics, provided with the Study Summary Sheet and asked to sign the Permission to Contact form. The researcher will contact those service users and arrange an appointment. During this appointment, service users will be screened for eligibility and, if eligible, provided with the Participant Information Sheet. Reasons for ineligibility for the trial will be recorded. Participants will be enrolled in the study, complete baseline assessments and be randomised to one of the conditions described below. Participants will be reimbursed £10 for their time.

### Intervention

Participants will continue to receive OAT (methadone or buprenorphine, including pro-longed release) as part of their treatment for OUD. Each participant will be randomly allocated (1:1) to receive one of two treatment allocations (mCM or TAU) over a 12-week period.

1mCM: App-based CM + OAT

Participants in this arm will receive financial incentives contingent on heroin-negative toxicology results. Over a 12-week period, participants will receive thrice-weekly (Monday, Wednesday, Friday) push notifications via the smartphone app when an oral saliva test is due. Smartphones with data plans will be provided to eliminate barriers to access. Participants will be required to conduct an oral saliva test and upload the result within a pre-specified time of receiving the push notification. Oral fluid test kits will be provided to the participants during appointments with the researcher. Participants will receive feedback upon submission, thanking them for uploading their video. The research team will review submissions upon receipt for quality and validity (self-testing and results adequately displayed). Verified heroin-negative tests will result in notification of earnings.

Reinforcer magnitude will be determined by consulting with the PPI group. We anticipate it will be approximately £5 for the first negative test result and escalate by £1 for each subsequent negative test to reach a maximum value of approximately £10. A ‘reset’ procedure will be used, whereby a missed or positive sample will result in a return to base rate for the next negative test. Earnings will be automatically loaded to the app wallet. Participants can access and spend vouchers from multiple vendors. Restrictions on spending categories can be applied, including alcohol, tobacco, and gambling.

The research team will systematically review sleep schedules, work patterns, and other routines with study participants, which could impose constraints on random testing. Schedules will be modified when necessary.

2TAU: Treatment As Usual

Participants will not receive the mCM intervention and will continue to receive OAT as usual.

### Outcomes

#### Feasibility trial outcomes.

The primary outcome of this feasibility trial is the number of eligible service users recruited over the 6-month recruitment period.

Secondary feasibility outcomes include:

The number and percentage of screened service users eligible for inclusion and reasons for ineligibility.The number and percentage of eligible service users who consent to participate in the feasibility trial and the reasons for refusing consent.Adherence to the intervention based on app interactions, responses to push notifications, and uploads.The number/percentage attending follow-up interviews of those randomised.The number/percentage of oral saliva tests uploaded of sufficient quality.The number/percentage of urine samples conducted (collected at four-weekly intervals following randomisation).Acceptability of the intervention among recipients exploring satisfaction and perceived benefits, assessed by qualitative interviews.Acceptability among treatment providers, exploring perceived appropriateness, intent for future adoption, and perceived positive or negative effects on service, assessed by qualitative interviews.

#### Clinical outcomes for a future confirmatory trial.

The primary clinical outcome measure for a future confirmatory trial is the percentage of heroin-negative urine samples (collected at four-week intervals following randomisation).

Secondary outcomes for the future confirmatory trial include:

Number/percentage retained in treatment over the 12-week intervention periodOpiate Treatment Index (Section 2 – Drug Use) [47]Hospital Anxiety and Depression Scale (HADS) [48]Social functioning measured using the Opiate Treatment Index [47]Stages of Change Readiness and Treatment Eagerness Scale (SOCRATES) [49]Other substance use: heroin and other substances (determined by urine immunoassays)

Items 2–6 will be collected at each assessment timepoint (baseline, weeks 4, 8, 12). We will also collect information needed to inform sample size calculations of the future confirmatory trial:

Appropriate summary statistics of the primary clinical outcome.

We will also collect information on:

Socio-demographic characteristics (including age, gender, ethnicity, employment status, living situation)

### Participant timeline and study visits

Participants will meet with the researcher at four time points: -t1 to complete baseline assessment, randomisation and enrolment and t1, t2 and t3 to provide bio-verified and self-reported assessment on drug use. Participants will be reimbursed £10 each time for their time. Recruitment is projected to take place between 1^st^ July 2025 and 31^st^ December 2025. See SPIRIT schedule of enrolment, interventions and assessments (Fig 1) and CONSORT diagram illustrating timeline and participant commitment (Fig 2).

**Fig 1 pone.0324516.g001:**
[figure not shown]
Spirit schedule of enrolment, interventions and assessment.

**Fig 2 pone.0324516.g002:**
[figure not shown]
CONSORT diagram illustrating timeline and participant commitment.

### Sample size

One of the aims of this feasibility trial is to estimate the parameters needed to inform a sample size calculation for the future confirmatory trial. A sample of 40 was chosen based on the resources available and the number required to estimate feasibility parameters with adequate precision. With 40 participants, we will be able to estimate the expected recruitment rate of 6.7 patients per month (primary feasibility outcome) to within a 95% confidence interval of 4.3 (4.8 to 9.1 patients recruited/month). For the second feasibility outcome (‘Percentage of screened patients eligible for inclusion and reasons for ineligibility’), we will be able to estimate the expected percentage of 50% to within a 95% confidence interval of 42% to 58%. This is based on screening 160 patients, of whom we expect 50% to be eligible, and of these, a half are expected to consent to participate.

### Randomisation

Participants will be randomly assigned to the two groups (mCM and TAU) using Sealed Envelope’s simple randomisation method, ensuring a 1:1 allocation ratio. The randomisation process will be straightforward and will not involve stratification or minimisation due to the small sample size. The details of the randomisation process will be documented and stored in the trial master file.

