### Progression criteria

Progression to a larger confirmatory trial will be evaluated based on the pre-specified progression criteria (see Table 1). However, not achieving ‘Green’ does not necessarily indicate the unfeasibility of a future trial but would indicate that changes are needed to recruitment procedures, attendance record keeping and follow-up resources.

**Table 1 pone.0324516.t001:** Pre-specified progression criteria.

	Green	Amber	Red
Number of eligible patients enrolled over the 6-month recruitment period	≥30, at least 15 per arm	≥20, at least 10/arm	<20
Percentage of screened patients who are eligible for inclusion in the feasibility trial.	≥50%;	≥30%;	<30%
Adherence to the intervention based on percentage of requested videos uploaded	≥70% in CM arm	≥50% in CM arm	<50% in CM arm
Percentage of urine drug screenings completed, overall	≥70% in all arms	≥50% in all arms	<50% in all arms
Number and percentage attending follow-up interview at end of 12-week intervention period (compared to number randomised)	≥70%	≥50%	<50%

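### Simple randomisation gives 1:1 only on average, and the per-arm minima in the recruitment progression row let chance allocation alone deny Green (8% of the time at 40 recruits, 31% at 35)

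*Protocol article*

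**What the plan says.** The Design and setting section states that "service users will be recruited and randomly assigned (1:1) to one of the conditions below". The Randomisation section names the method as a "simple randomisation method, ensuring a 1:1 allocation ratio" and adds that the process "will not involve stratification or minimisation due to the small sample size". It mentions no blocking.

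The Outcomes section defines the primary feasibility outcome as a total: the number of eligible service users recruited in six months. Table 1 (Progression criteria) grades the same quantity, "Number of eligible patients enrolled over the 6-month recruitment period", but adds an arm-level condition. Green is "≥30, at least 15 per arm", Amber is "≥20, at least 10/arm", and Red is a total below 20 with no arm condition.

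The Sample size section says "A sample of 40 was chosen based on the resources available" and on precision. The Data collection section plans qualitative interviews with 20 participants who received the intervention, which is the whole mCM arm under an exact 20/20 split.

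**The concern.** In its ordinary meaning, simple randomisation is a series of independent 50:50 assignments. It fixes the probability of each assignment, not the final arm sizes, so it cannot ensure a ratio.

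The wording matters because Table 1 depends on arm sizes. Each per-arm minimum is exactly half its total threshold, so at 30 recruits only 15/15 is Green and at 20 recruits only 10/10 is Amber. Arm size is produced by the randomiser and says nothing about whether service users can be recruited. A downgrade for that reason would still be read as Table 1's introduction reads any missed Green, namely as a sign that procedures such as recruitment need changing.

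The categories also leave a gap. A total of 20 or more with one arm below 10 meets neither Green nor Amber, and it is not Red.

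**Working it through.** **Inputs.** Target N = 40 (Sample size); allocation probability 0.5 per person (Design and setting, Randomisation); Green and Amber minima of 15 and 10 per arm (Table 1); six months of recruitment (Recruitment).

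**The plan's own figure.** 40/6 = 6.67 per month. The exact Poisson 95% interval for a count of 40, divided by 6, is 4.76 to 9.08, width 4.32. This reproduces the stated precision, "to within a 95% confidence interval of 4.3 (4.8 to 9.1 patients recruited/month" being the plan's rounding. Over six months the stated limits correspond to 4.8 × 6 = 28.8 and 9.1 × 6 = 54.6, or about 29 to 55 recruits. Totals in the low 30s are therefore within the plan's own range.

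**Does simple randomisation ensure 1:1?** Let X be the size of one arm, X ~ Binomial(40, 0.5).
- P(X = 20) = C(40,20)/2^40 = 12.5%.
- P(16/24 or more unequal) = 2 × P(X ≤ 16) = 26.8%.
- P(mCM arm below 20) = P(X ≤ 19) = 43.7%.

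**Chance that a per-arm minimum fails.** For total N and minimum m, P(fail) = 1 − Σ C(N,x)/2^N, summed over x = m to N − m. At N = 30, m = 15, only x = 15 passes: C(30,15)/2^30 = 14.4%, so failure is 85.6%. At N = 20, m = 10, only x = 10 passes: C(20,10)/2^20 = 17.6%, so failure is 82.4%.

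| Total N | Green minimum (15) fails | Amber minimum (10) fails |
|---|---|---|
| 20 | not applicable | 82.4% |
| 25 | not applicable | 23.0% |
| 30 | 85.6% | 4.3% |
| 32 | 59.7% | 2.0% |
| 35 | 31.1% | 0.6% |
| 38 | 14.3% | 0.17% |
| 40 | 8.1% | 0.07% |

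**Averaging over the total.** The protocol gives no distribution for the total, so I assume a Poisson count capped at 40 and weight the failure probabilities by it.
- Mean 40: a total of at least 30 with an arm below 15 occurs in about 18% of trials. A total of at least 20 with an arm below 10 (no category) occurs in about 1%.
- Mean 35: the figures are about 26% and 4%.

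**Would blocks cure it?** With permuted blocks of 2, 4 or 6, both arms reach 15 with certainty at N = 40. At the thresholds this is not assured. Blocks of 4 at N = 30 leave a half-filled last block, and the split is 15/15 with probability 0.667, so Green is missed one time in three. Blocks of 6 at N = 20 meet the Amber minimum with probability 0.60.

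**The case against.** The strongest reply is about size. At the planned 40, the Green clause fails 8% of the time and the Amber clause almost never. Under the Poisson assumption with mean 40, exactly 30 recruits has probability 1.8% and exactly 20 has 0.02%. A reader might infer from the table's first figures that Green or Amber will usually be lost by chance. The documents do not support that, because 86% and 82% hold only at those exact totals. This part of the reply stands, and it lowers the severity.

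Second, Table 1's introduction says that missing Green does not of itself show a future trial to be unfeasible, and the Data analysis section makes between-arm estimates exploratory. A reader might infer that a bad split stops the programme or spoils a test; neither follows. But the same introduction treats a missed Green as a sign that procedures need changing, which is the wrong lesson when the cause is allocation.

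Third, a reader might infer that the small sample is wrongly offered as a reason for simple randomisation. The sentence gives it only as the reason for omitting stratification and minimisation, which is defensible at 40. It simply does not bear on blocking.

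Fourth, a reader might infer that imbalance always costs precision in the mCM-only estimates. It does not: the mCM arm exceeds 20 as often as it falls short. Relative to 20, an arm of 16 raises the standard error by a factor of √(20/16) = 1.12, and an arm of 24 changes it by √(20/24) = 0.91. What does stand is narrower: the 20 planned recipient interviews need an mCM arm of at least 20.

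Finally, simple randomisation is unpredictable, which has value here because the research team is unblinded and the randomisation takes place at the researcher's baseline visit. That is a fair reason to keep it, but not a reason to say that it ensures 1:1 or to tie the recruitment grade to arm size.

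**Conclusion.** The point holds and should be fixed, though it is not critical. The statement that simple randomisation ensures 1:1 is wrong as written. The recruitment row grades a total by a condition that chance allocation can break: 8% of the time at 40 recruits, 31% at 35, 60% at 32, and about 18% overall under Poisson recruitment with mean 40 capped at 40 (26% with mean 35). The Amber minimum matters in practice only if the total falls to the 20s, and there the row can leave a trial without a category. The interview target of 20 recipients would be out of reach 44% of the time at 40 randomised.

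The binomial figures assume that simple randomisation means independent 50:50 assignment. The article places further details in the trial master file. If the service in fact uses blocks, these probabilities no longer apply, but then the word simple is wrong and the sentence still needs correcting. The overall percentages also rest on the Poisson assumption, which is mine.

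**What to change.** 1. In the Randomisation section, delete the claim that simple randomisation ensures 1:1; say that allocation is 1:1 in expectation, or change the method.
2. In Table 1, base the recruitment row on total enrolment alone: Green ≥30, Amber 20-29, Red <20. This removes both the chance downgrade and the uncategorised case, whatever the randomisation method.
3. In addition, or instead if a minimum arm size is wanted (for example so that upload adherence rests on enough people), use unstratified permuted blocks of varying, concealed size on the same service. If the per-arm minima stay, state which grade applies when the total is sufficient but an arm is short, since blocks may not guarantee the minima at exactly the threshold.
4. State the interview target as up to 20, or as all willing mCM recipients, unless the allocation method secures an arm of 20.

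Cost: items 1, 2 and 4 are wording changes in a short amendment. Item 3 is a setting on the randomisation service, best made before the first allocation, since past allocations cannot be rebalanced. Its downside is predictability: with known blocks of 2 or 4 the unblinded team could guess correctly about 75% or 71% of the time, against 50% under simple randomisation. Very small blocks should therefore be avoided and sizes kept from recruiters. Stratifying by site is optional and is not needed to resolve this point.
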